## Abstract

**Background:**

Lung cancer, predominantly non-small cell lung cancer (NSCLC), remains a formidable challenge, necessitating an in-depth understanding of evolving treatment paradigms. The Italian Lung Cancer Observational Study (LUCENT) addresses this need by investigating the outcomes of patients with early and locally advanced lung cancer in Italy.

**Objective:**

With a focus on real-world data and patient registries, this study aims to provide comprehensive insights into clinical, psychosocial, and economic impacts, contributing to informed decision-making in health care.

**Methods:**

LUCENT is a prospective observational multicenter cohort study enrolling patients eligible for minimally invasive manual, robot-assisted, or traditional open surgery. The study will develop a web-based registry to collect longitudinal surgical, oncological, and socioeconomic outcome data. The primary objectives include performance assessment through the establishment of national benchmarks based on risk-adjusted outcomes and processes of care indicators. The secondary objectives encompass economic and psychosocial impact assessments of innovative technologies and treatment pathways. The multicenter design ensures a diverse and representative study population.

**Results:**

The evolving landscape of NSCLC treatment necessitates a nuanced approach with consideration of the dynamic shifts in therapeutic strategies. LUCENT strives to fill existing knowledge gaps by providing a platform for collecting and analyzing real-world data, emphasizing the importance of patient-reported outcomes in enhancing the understanding of the disease. By developing a web-based registry, the study not only facilitates efficient data collection but also addresses the limitations of traditional methods, such as suboptimal response rates and costs associated with paper-and-pencil questionnaires. Recruitment will be conducted from January 01, 2024, to December 31, 2026. Follow-up will be performed for a minimum of 2 years. The study will be completed in the year 2028.

**Conclusions:**

LUCENT’s potential implications are substantial. Establishing national benchmarks will enable a thorough evaluation of outcomes and care processes, guiding clinicians and policymakers in optimizing patient management. Furthermore, the study’s secondary objectives, focusing on economic and psychosocial impacts, align with the contemporary emphasis on holistic cancer care. Insights gained from this study may influence treatment strategies, resource utilization, and patient well-being, thereby contributing to the ongoing refinement of lung cancer management.

**Trial Registration:**

ClinicalTrials.gov NCT05851755; https://clinicaltrials.gov/study/NCT05851755. ISRCTN 67197140; https://www.isrctn.com/ISRCTN67197140

**International Registered Report Identifier (IRRID):**

PRR1-10.2196/57183

## Introduction

### Background and Rationale

Most lung cancer cases involve non-small cell lung cancer (NSCLC), while small cell cancer represents the minority of cases. To date, limited percentages of NSCLC cases are diagnosed in the early stage (in which patients are potential candidates for surgery, possibly followed by chemotherapy, to reduce the risk of recurrence) or in the locally advanced stage (in which the treatment is based on the use of chemotherapy, radiotherapy, and possibly, upon their completion, immunotherapy). The therapeutic strategy in patients with advanced NSCLC has changed in recent years. Until about 10 years ago, chemotherapy was the only option available; however, it was characterized by limited effectiveness. In recent years, the 2 crucial therapeutic “revolutions” we have witnessed in medical oncology (molecularly targeted drugs and then immunotherapy) have played essential roles in treating these patients. Some molecularly targeted drugs (primarily epidermal growth factor receptor [EGFR] inhibitors and then drugs directed against other molecular alterations) are superior to chemotherapy as a first-choice treatment, but the use of these drugs is limited to cases in which the tumor has those specific molecular alterations. Molecular analyses aimed at identifying these alterations in the tumor tissue represent a fundamental part of the diagnosis, which precedes the best treatment choice for each patient. In the next few years, we will probably see the continuation of those therapeutic “revolutions” mentioned above with the availability of new molecularly targeted drugs. These approaches will increase the therapeutic possibilities to be used in sequence after the failure of the approaches already available today [1]. Still, in some cases, they will allow a “targeted” treatment in the presence of molecular alterations for which no target drugs are available in clinical practice until now. Immunotherapy first established itself (about 5 years ago) as an effective treatment in patients who had already failed chemotherapy [1]. Subsequently, it was proven to be superior to chemotherapy as the first-choice treatment in cases characterized by high expression of the PD-L1 marker. Finally, significant results have been obtained in recent years by combining chemotherapy and immunotherapy, even in patients with low or absent PD-L1 expression. It is conceivable that in the coming years, based on a series of clinical trials recently conducted or still in progress, innovative drugs (targeted therapies and immunotherapy) will have essential roles in the treatment of early stages of cancer (used before surgery or after surgery) to reduce the risk of disease recurrence and hopefully increase the chances of recovery. The 5-year survival rate of lung cancer is low (16% in men and 23% in women), and it is at the bottom of the survival ranking, reminding us that, despite the critical progress made in recent years, there is a long way ahead regarding its treatment [2-4].

Globally, there is an increasing trend to use real-world data to inform decision-making in health care, and patient registries are regarded as a typical example of real-world data. A patient registry can be defined as “an organized system that uses observational study methods to collect uniform data (clinical and other) to evaluate specified outcomes for a population defined by a particular disease, condition, or exposure, and that serves one or more predetermined scientific, clinical, or policy purposes” [5,6]. While regulatory agencies can use real-world data collection for postmarketing surveillance and risk assessment, payers and reimbursement agencies are consistently considering real-world evidence to make or revise their recommendations. To this end, the information collected in patient registries can extend from appropriate treatment strategies to effectiveness and cost-effectiveness assessments in real-world clinical practice [7,8].

Furthermore, achieving and maintaining optimal well-being and health-related quality of life (HRQoL) have become essential objectives of cancer treatment, rehabilitation, and aftercare across the cancer continuum. The availability of patient-reported outcomes (PROs) is critical in achieving these goals. In the past, patient registries have provided clinicians and researchers with a wealth of clinical data (eg, stage and primary treatment) on cancer patients. However, data on PROs are not yet routinely available. PROs have been collected using paper-and-pencil questionnaires, with suboptimal response rates, high costs, and overall process efficiency. Online administration of questionnaires has several advantages compared with paper-and-pencil questionnaires, including convenience for the participant, potentially significant cost savings, data collection efficiency, and high data quality [9-12].

Therefore, we propose to develop a web-based registry to collect longitudinal data on the clinical, psychosocial, and economic impacts of lung cancer treatment in Italy.

### Objectives

#### Primary Objectives

The project involves a web-based registry developed to facilitate data collection and evaluation of several different surgical, oncological, and socioeconomic outcomes of lung cancer patients diagnosed in early and locally advanced stages in Italy.

The primary objective is to generate data relevant to performance assessment through the development of national performance benchmarks based on the analysis of risk-adjusted outcomes and the processes of care indicators (eg, How does individual center X compare to the national standard in terms of length of stay for a certain subgroup of patients?).

#### Secondary Objectives

The registry can be used simultaneously for multiple studies with different purposes. Among the secondary objectives are the following: (1) Economic impact assessment of innovative technologies or treatment pathways (eg, Do different surgical medical devices influence health care resource utilization for a single episode of hospitalization?) and (2) Psychosocial impact assessment of innovative technologies or treatment pathways, for example, minimally invasive surgery (eg, Do new targeted treatments have a beneficial or adverse impact on PROs?).

### Trial Design

The Italian Lung Cancer Observational Study (LUCENT) is a prospective observational multicenter cohort study enrolling lung cancer patients who are candidates for minimally invasive manual, robot-assisted, or traditional open surgery. This study aims to investigate the outcomes of patients with early and locally advanced lung cancer in Italy. By using real-world data and patient registries, the study seeks to provide comprehensive insights into the clinical, psychosocial, and economic impacts of lung cancer treatment. The study’s observational nature allows for data collection in a naturalistic setting without intervention or manipulation by the researchers. The list of collaborating institutions has been provided in Multimedia Appendix 1.

## Methods

### Study Setting

This multicenter study will include community clinics and academic centers located in Italy. This protocol has been presented in compliance with the SPIRIT (Standard Protocol Items: Recommendations for Interventional Trials) checklist [13].

### Eligibility Criteria

#### Inclusion Criteria

The inclusion criteria are as follows:

Diagnosis of lung cancer: Patients must meet the following criteria for the diagnosis of lung cancer: (1) confirmation of lung cancer through histopathological examination or imaging studies and (2) specific ICD-10 codes for lung cancer that include but are not limited to C34.0 (main bronchus), C34.1 (upper lobe, lung), C34.2 (middle lobe, lung), C34.3 (lower lobe, lung), C34.8 (overlapping lesion of the lung), and C34.9 (lung, unspecified).Age criteria: Patients must be aged 18 years or older at the time of enrollment.Informed consent: Patients must provide written informed consent to participate in the study.Communication requirement: Patients should provide an email address at the time of enrollment for follow-up communication and the exchange of questionnaires.Language proficiency: Patients should be able to understand and communicate in Italian.

#### Exclusion Criteria

The exclusion criteria are as follows:

Language proficiency: Patients are unable to understand or communicate in Italian.

### Who Will Take Informed Consent?

Qualified health care professionals will conduct the informed consent process at each participating institution in this study. These professionals will ensure that potential participants are fully informed about the study’s purpose, procedures, and possible risks and benefits, and their rights as participants. They will also address any questions or concerns raised by the participants and obtain written informed consent from those who voluntarily choose to participate in the study. The informed consent process will adhere to ethical guidelines and regulatory requirements to safeguard the rights and well-being of the participants.

### Additional Consent Provisions for the Collection and Use of Participant Data and Biological Specimens

We will conduct the trial according to the ICH Good Clinical Practice (GCP) guidelines. Accurate and consistent records are essential to a cooperative study.

The clinical and surgical data collected in a standardized endorsed data set can be downloaded locally and used for internal quality analyses or institutional research. The data collection methodology will use a website platform that meets international data privacy protection standards and rules. Notably, data are anonymously reported, independently accessed, and encrypted for other users.

For joining the database, the login of each institution will be provided after downloading and completing an application form from the project homepage and directly sending an email to the study coordinator. Investigators will access the patient medical records and enter the required data into the database. Protected health information will not be reused or disclosed to any other person or entity, except as required by law, for authorized research project oversight.

In compliance with the ICH-GCP guidelines, the investigator or institution will maintain all electronic case report forms, all source documents that support the data collected from each subject, all study documents as specified in ICH-GCP Section 8 (Essential Documents for the Conduct of a Clinical Trial), and all study documents as determined by the applicable regulatory requirements. The investigator or institution will take measures to prevent accidental or premature destruction of these documents. Essential documents must be retained until at least 25 years after the last approval of a marketing application in an ICH region and until there are no pending or contemplated marketing applications in an ICH region or until at least 15 years have elapsed since the formal discontinuation of clinical development of the investigational product. These documents will be retained longer if required by the applicable regulatory requirements or an agreement with the sponsor. The sponsor is responsible for informing the investigator or institution when these documents no longer need to be retained.

If the responsible investigator retires, relocates, or withdraws from the responsibility of keeping the study records for other reasons, custody must be transferred to a person who will accept the duty. The sponsor must be notified in writing of the name and address of the new custodian. Under no circumstance shall the investigator relocate or dispose of any study documents before obtaining written approval from the sponsor. If it becomes necessary for the sponsor or the appropriate regulatory authority to review any documentation relating to this study, the investigator must permit access to such reports.

### Interventions

#### Explanation for the Choice of Comparators

The choice of comparators in this study is driven by the need to assess and compare various surgical interventions for lung cancer patients. The study aims to enroll patients eligible for minimally invasive manual, robot-assisted, or traditional open surgery, reflecting the diverse landscape of surgical approaches in clinical practice.

The rationale for including these comparators is rooted in the evolving nature of lung cancer treatment, where different surgical modalities are employed based on factors such as tumor characteristics, patient condition, and advancements in surgical techniques. Minimally invasive surgeries, including robot-assisted procedures, have gained prominence for their potential benefits, such as reduced postoperative pain, shorter hospital stay, and quicker recovery compared to traditional open surgery.

By including these comparators, this study seeks to evaluate and compare the outcomes of these diverse surgical interventions. This comprehensive approach allows for a nuanced understanding of the effectiveness and potential differences in results associated with each surgical modality. It also enables the study to contribute valuable insights into the evolving landscape of lung cancer treatment, guiding future clinical decisions and optimizing patient care.

The choice of comparators aligns with the study’s overarching objective to generate data for performance assessment. This provides a basis for national benchmarks and facilitates a thorough analysis of outcomes and care processes. This approach ensures that the study captures the diversity of surgical practices in the real-world setting, reflecting the dynamic nature of lung cancer treatment and contributing to the broader knowledge base in the field.

#### Intervention Description

The interventions in this study encompass a spectrum of surgical approaches for lung cancer patients diagnosed in the early and locally advanced stages.

Regarding the rationale for intervention selection, the choice of interventions reflects the diversity of surgical practices in treating lung cancer. Each intervention has its advantages and considerations, and the study aims to evaluate and compare their outcomes comprehensively. Including minimally invasive and robot-assisted surgeries acknowledges the evolving landscape of surgical techniques, aligning with the contemporary emphasis on reducing patient morbidity and improving recovery.

Patients meeting the inclusion criteria will be assessed for eligibility, and the choice of intervention will be based on factors such as tumor characteristics, patient condition, and the surgeon’s expertise.

Qualified and experienced health care professionals will perform the surgical procedures at participating institutions. Data related to the interventions, perioperative details, and postoperative outcomes will be systematically collected through the web-based registry developed for the study.

### Criteria for Discontinuing or Modifying Allocated Interventions

The criteria for discontinuing or modifying allocated interventions in LUCENT are established to ensure participants’ safety and well-being while maintaining the study’s integrity. These criteria are designed to address unforeseen circumstances, emerging patient-related factors, or changes in clinical status. The discontinuation or modification of interventions will be considered under the following events:

Medical emergencies: If a participant experiences a medical emergency during or after the intervention, the allocated intervention may be discontinued or modified to address the emergent health situation. The treating health care professionals will decide on the situation and prioritize the participant’s health and safety.Adverse events (AEs): In the case of unexpected AEs related to the allocated intervention, the study protocol allows for the discontinuation or modification of the intervention to mitigate potential harm to the participant. AEs will be monitored, documented, and reported according to the study’s safety monitoring procedures.Participant withdrawal: If a participant chooses to withdraw from the study or requests a change in the allocated intervention, their decision will be respected. Withdrawal may be due to personal reasons, differences in health status, or other factors influencing the participant’s willingness to continue with the allocated intervention.Protocol deviation: Any deviation from the study protocol deemed necessary for the participant’s well-being may lead to modification or discontinuation of the allocated intervention. Protocol deviations will be documented and reported according to the study’s data management and reporting procedures.Clinical judgment: Health care professionals, in consultation with the principal investigator, may exercise clinical judgment to modify or discontinue the allocated intervention if unforeseen clinical circumstances arise that warrant such actions. Decisions will be made based on the best interests of the participant and in adherence to ethical and safety considerations.Loss to follow-up: If a participant loses access to follow-up or cannot adhere to the scheduled assessments and interventions, modifications may be considered based on the available information. It is crucial to note that any discontinuation or change of allocated interventions will be thoroughly documented, and the reasons for such actions will be reported in the study records. Additionally, these decisions will be communicated to relevant stakeholders, including the study participants and institutional review boards, ensuring transparency and adherence to ethical standards. The criteria outlined aim to balance participant safety with the scientific rigor of the study.

### Strategies to Improve Adherence to Interventions

The following strategies will be implemented to optimize and enhance adherence throughout the study:

Patient education and informed consent: Clear and comprehensive education about the study, its purpose, and the importance of adherence will be provided during the informed consent process.Multidisciplinary team engagement: A multidisciplinary health care team, including surgeons, nurses, and support staff, will be involved in patient education and engagement.Regular communication: Normal communication channels will be established between health care providers and participants to address any concerns, provide ongoing support, and reinforce the importance of adherence.Patient-centered decision-making: Patients will be involved in decision-making regarding their treatment to foster a sense of autonomy and ownership in the intervention process.Monitoring and feedback: A robust monitoring system will be implemented to track participant progress and intervention adherence.Patient support programs: Support programs, including psychological support and resources, will be offered to address the emotional and psychological aspects of the intervention.Use of technology: Technology, such as mobile apps or online platforms, will be leveraged to provide educational materials, reminders, and real-time support.Continuous participant engagement: Strategies will be implemented to maintain participant engagement throughout the study, including newsletters, educational materials, and updates on study progress.

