### Relevant Concomitant Care Permitted or Prohibited During the Trial

Adherence to interventions is crucial for scientific validity and participant well-being. The following strategies will be implemented to optimize adherence throughout the study: clear and comprehensive education during informed consent, and emphasizing the study’s purpose and the importance of adherence. Patients will be informed about the potential benefits, highlighting their contribution to advancing knowledge in lung cancer treatment. A multidisciplinary health care team, including surgeons, nurses, and support staff, will be involved in patient education and engagement. A collaborative approach ensures consistent information and support from various health care professionals. Treatment plans will be tailored to individual patient needs and preferences to enhance buy-in and motivation to adhere to the protocol. Patient-specific factors, such as lifestyle and cultural background, can improve adherence. Regular communication channels will be established between health care providers and participants to address concerns, provide ongoing support, and reinforce the importance of adherence. Telehealth or virtual platforms will be implemented for follow-up consultations to facilitate continuous communication. Patients will be included in decision-making to foster a sense of autonomy and ownership in the intervention process. Shared decision-making can enhance commitment and adherence to the chosen intervention. A robust monitoring system will be implemented to track participant progress and adherence. Timely feedback will be provided to participants on their progress. Acknowledgment of their contributions is considered positive reinforcement. Support programs, including psychological support and resources, will be offered to address the emotional and psychological aspects of the intervention. Support programs help patients to cope with challenges, fostering a positive attitude toward the intervention. Technologies, such as mobile apps and online platforms, will be adopted to provide educational materials, reminders, and real-time support. Technology can enhance engagement and facilitate communication between participants and health care providers. Flexibility will be offered in scheduling interventions to accommodate individual participant preferences and logistical considerations. Flexible scheduling can reduce barriers to adherence and increase overall participant satisfaction. Strategies will be implemented to maintain participant engagement, including newsletters, educational materials, and updates on study progress. This will ensure that participants feel connected and valued as contributors to the research endeavor.

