
### Provisions for Posttrial Care

The provisions for posttrial care in LUCENT are designed to ensure that participants receive appropriate medical attention and support even after their active involvement in the study has concluded. The posttrial care plan prioritizes the well-being of participants and addresses any ongoing medical needs that may arise. The key provisions for posttrial care include the following:

Continuity of standard medical care: Participants will continue to receive standard medical care for lung cancer as per established clinical guidelines, irrespective of their involvement in the study. The study team will facilitate the seamless transition of participants back to routine medical care provided by their health care providers.Access to study-related information: Participants will continue to have access to information related to the study, including summaries of study results, as they become available and appropriate for dissemination.Follow-up assessments: If any scheduled follow-up assessments or evaluations are part of the study protocol extending beyond the active trial period, participants will be informed about and encouraged to attend these follow-up appointments.AE monitoring: During the posttrial period, the study team will continue to monitor and address any AEs or complications related to the study interventions or procedures.Referral to specialists: If participants require specialized care or additional medical attention beyond the scope of the study, appropriate referrals to specialists will be facilitated.Communication and support: Participants will be provided with the contact information of the study team or a designated point of contact, allowing them to reach out with any questions or concerns about their participation or posttrial care.Emergency procedures: Clear procedures will be in place to manage any emergent medical situations that participants may face after the conclusion of the trial, with appropriate guidance on seeking urgent medical attention. The posttrial care provisions emphasize the ethical responsibility of the study team to prioritize participant welfare beyond the active study period. By providing ongoing support, access to information, and coordination with standard medical care, the study aims to ensure a comprehensive and ethical approach to the well-being of participants even after their active involvement in the observational study has ended.

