#### Additional Outcomes and Considerations

The additional outcomes and considerations are as follows:

Longitudinal clinical outcomes: (1) Analysis of long-term clinical outcomes related to the chosen surgical interventions; and (2) Evaluation of recurrence rates, overall survival, and disease-free survival among participants.PROs: (1) Collection of PROs related to well-being, quality of life, and psychosocial factors; and (2) Utilization of online administration of questionnaires to enhance efficiency and data quality.Health care resource utilization: (1) Examination of the utilization of health care resources, including hospital stay, postoperative care, and associated costs; and (2) Identification of factors influencing resource utilization and potential areas for improvement.Treatment decision patterns: (1) Analysis of the patterns in treatment decisions, considering factors such as tumor characteristics and patient preferences; and (2) Exploration of the factors influencing the choice of surgical interventions.Patient characteristics and demographics: (1) Documentation of patient demographics, including age, gender, and other relevant characteristics; and (2) Analysis of how patient characteristics may influence treatment outcomes and decision-making.AEs and complications: Monitoring and documentation of AEs and complications related to the chosen interventions; and (2) Evaluation of the safety profile of different surgical modalities.

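### The observational design excludes researcher intervention, yet psychological support is listed as a study adherence strategy and is not stated to be usual care

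*Protocol article*

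**What the plan says.** Trial Design presents LUCENT as a prospective observational cohort with "data collection in a naturalistic setting without intervention or manipulation by the researchers".

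Strategies to Improve Adherence to Interventions opens its list with "The following strategies will be implemented to optimize and enhance adherence throughout the study". One item reads "Support programs, including psychological support and resources, will be offered to address the emotional and psychological aspects of the intervention".

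The next section, headed as dealing with concomitant care, repeats most of the list and adds two statements that matter here. On the effect expected of the support: "Support programs help patients to cope with challenges, fostering a positive attitude toward the intervention". On treatment: "Treatment plans will be tailored to individual patient needs and preferences to enhance buy-in and motivation to adhere to the protocol".

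On outcomes, Secondary Objectives includes psychosocial impact. Additional Outcomes and Considerations includes "Collection of PROs related to well-being, quality of life, and psychosocial factors" and, under treatment decision patterns, "Exploration of the factors influencing the choice of surgical interventions". Table 1 schedules health-related quality of life at baseline and at follow-up. Statistical Methods names the EQ-5D-5L, with anxiety/depression as one of its five dimensions.

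**The concern.** A registry that reports real-world PROs needs the care behind them to be the care patients would have received anyway. Most of the listed strategies, such as reminders, newsletters and study updates, serve data collection and raise no difficulty. Psychological support is different, because it is directed at the patient's emotional state, and the registry also measures psychosocial outcomes. If centers read the list as an instruction and add or extend support because of the study, the registry would describe quality of life under that support and label it usual practice.

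At stake are the reported level of the PROs and their change from baseline. The sentence on tailoring raises a smaller question of the same kind: an observational registry has no treatment protocol for patients to adhere to, so protocol adherence is an odd reason for shaping a treatment plan.

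**Working it through.** No arithmetic applies. The article states no figure on this point, and it gives neither the proportion of patients who would take up support nor its effect on any PRO, so a shift cannot be calculated. The check is a comparison of the text.

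1. **Is there a commitment?** Yes. "The following strategies will be implemented to optimize and enhance adherence throughout the study" is a statement of what the study will do, and it introduces the support item. The item itself says the support will be offered.

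2. **Is the item about data collection or about care?** About care. The stated target is the emotional and psychological side of the intervention, and the stated effect is "Support programs help patients to cope with challenges, fostering a positive attitude toward the intervention". Retention in follow-up has its own list under Data Collection and Management (reminders, study updates, a coordinator, flexible visits), so the support item is not needed for that purpose.

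3. **Does any section limit the support to existing services?** None found. The adherence sections do not name the supplier. Provisions for Posttrial Care says that standard lung cancer care continues whether or not the patient takes part, but it does not mention psychological support during the study.

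4. **Does the support fall inside the measured interval?** Yes. The strategies run throughout the study, and quality of life is measured at baseline and again at follow-up.

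5. **Is there a path to a study outcome?** Yes, by inference. Coping and attitude lie close to the psychosocial factors in "Collection of PROs related to well-being, quality of life, and psychosocial factors" and to the anxiety/depression dimension. The article does not say that the support changes the EQ-5D-5L index. Only the intended direction can be read from the text: better coping would tend to make PROs look better than under usual care alone.

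6. **Which objectives are touched?** Psychosocial impact and PROs are secondary or additional. The primary objective is national benchmarks from risk-adjusted outcomes and process indicators, with length of stay as the example. Nothing in the text links the support to those.

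7. **The tailoring sentence.** Fitting a plan to needs and preferences is ordinary care, and patient preferences are among the factors the registry intends to study. Intervention Description bases the choice of surgery on factors such as the tumor, the patient's condition and the surgeon's expertise. The only part that does not fit is the purpose given at the end of "Treatment plans will be tailored to individual patient needs and preferences to enhance buy-in and motivation to adhere to the protocol".

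**The case against.** The strongest reply is that the contradiction needs an actor whom the text does not name. Trial Design excludes intervention by researchers, whereas the adherence sections speak of health care teams and providers, and the support sentence is passive. If centers simply point patients to their existing psycho-oncology services, nothing is added to usual care. The Discussion reports no external funding and possible limits on resources, which makes a study-supplied program less likely. The wording also resembles template text for an interventional trial.

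Much of this stands. It means that a study-run psychological intervention is not established, only that the text commits to support as a study strategy and leaves its status open. It does not remove the conflict: centers and ethics committees act on what is written, and what is written is a study strategy for adherence.

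A reader might go further in three ways that the document does not support.

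- **Bias between surgical approaches.** Nothing ties the support to open, manual minimally invasive or robot-assisted surgery.
- **Distorted treatment decisions.** The tailoring sentence does not say that the surgical approach would change, and what remains is one clause about motive.
- **Non-routine care during the study**, inferred from "The study team will facilitate the seamless transition of participants back to routine medical care provided by their health care providers". That is a turn of phrase in a section on post-trial care, and it stands beside an explicit statement that standard care continues irrespective of participation. It is too thin to carry the point.

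**Conclusion.** The point holds in a limited form. The article states a design property, no intervention by the researchers, and then lists psychological support as a study adherence strategy without saying that it is usual care. As written, the plan does not secure the property it claims.

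The consequence is a possible shift in the level and change of the PROs that the registry would describe as real-world. Its size is unknown. It depends on two assumptions that the document neither confirms nor excludes: that some centers would provide support beyond their usual practice because of the study, and that such support affects the PROs measured. The adherence purpose attached to tailoring is a minor inconsistency of wording. This is worth correcting because the correction is nearly free.

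**What to change.** In the two sections that list adherence strategies:

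- Limit the measures to retention in follow-up and completion of questionnaires, in line with the retention list under Data Collection and Management.
- Delete the closing clause of the tailoring sentence, which gives buy-in and protocol adherence as its purpose.
- Add one sentence stating that treatment choice, treatment plans and psychological support follow each center's usual care.

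If the sponsor does want a study-supplied support package, say so in Trial Design, offer it uniformly at all centers, and record for each patient whether it was received. PRO results should then be described as obtained under that support.

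The cost is protocol wording and an ethics amendment. Keeping the package adds one descriptive variable per patient. Neither route needs extra patients.
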